##### Early OMIs group

On the basis of routine care, we will implement an oral motor intervention program developed by American researcher Fucile, adapted for the Chinese context made by the domestic expert, Lv et al. [7, 15]. The program includes oral stimulation, which involves stimulation of the lips, cheeks, gums, and tongue, along with non-nutritive sucking. The intervention will start once the infant begins to receive milk and exhibits stable vital signs. It will be conducted once a day, for 15 min at a time, and will continue until the infant reaches full oral feeding and maintains it for 48 h without the need for tube feeding. The timing of each intervention is set for 15–30 min before any feeding session, within the hour of 8:00–18:00. All interventions will be performed by charge nurses who have received uniform training. If the infant experiences changes in their condition such as decreased oxygen saturation, bradycardia, or asphyxia, the intervention will be stopped.

##### Late OMIs group

The interventions for OMIs will be initiated 48 h following the discontinuation of nasal continuous positive airway pressure. The early OMIs group and the late OMIs are the same in every aspect, with the sole distinction being the difference in the start time.

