**Methods:**

This is a single-blind, randomized controlled trial. Preterm with a gestational age between 29^+0^ to 34^+6^ weeks will be eligible for the study. These infants will be randomized and allocated to one of two groups, both of which will receive the OMIs. The intervention commences once the infant begins milk intake during the early OMIs. Additionally, in the late OMIs group, the intervention will initiate 48 h after discontinuing nasal continuous positive airway pressure.

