### Eligibility criteria {10}

Inclusion criteriaDiagnosis as preterm, with a birth weight of less than 2500 g, and gestational age ranging from 29^+0^ to 34^+6^ weeks.Stability of vital signs.Absence of major congenital anomalies, such as congenital heart disease, or congenital digestive tract malformations.Requirement non-invasive ventilation support, including the use of a high-flow nasal cannula.Enrollment within the first 72 h of life.

Exclusion criteriaRequirement of mechanical ventilation.Severe asphyxia.Prior enrollment in other studies.Diagnosis of necrotizing enterocolitis (NEC).Diagnosis of periventricular leukomalacia (PVL).Diagnosis of intracranial hemorrhage grade III or higher.Need for reinitiation of non-invasive ventilation support after the start of the OMIs.

There are termination criteria and they are as follows: (1) Occurrence of severe adverse events and complications during the trial. (2) Withdrawal of consent by the parents of the subject. Patients who enter the trial but fail to complete it due to any reason will be considered dropout cases. This includes cases where the doctor determines that the subject has withdrawn from the trial, as well as cases where the subject withdraws on their own, regardless of the timing or reason for withdrawal. All data on the infants will still be recorded.

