#### Strategies to improve adherence to interventions {11c}

Every possible endeavor will be undertaken to maintain the authenticity of the intervention. Before the study begins, individuals participating in the research will receive standardized training in accordance with the research manual. Only after passing the assessment will they be allowed to join the study. Any divergence from the protocol will be meticulously recorded, with an intervention fidelity checklist being completed by the research nurse at the conclusion of the procedure.

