**Table 2 Tab2:**
[figure not shown]
Study timeline

t1 started to feed; t2 after 48 h of discontinuing non-invasive ventilation; t3 full oral feeding; t4 discharge; t5 follow-up at 6 months after discharge; t6 follow-up at 12 months after discharge; t7 at the corrected age of 18–22 months

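### The late arm starts 48 h after nasal CPAP in the operative text but 48 h after non-invasive ventilation elsewhere, so eligible high-flow-only infants have no start date

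*Protocol article*

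**What the plan says.** The start of the late arm is described in five places in the protocol article, and they use two different triggers.

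- **Nasal CPAP.** The section on the late OMIs group reads "The interventions for OMIs will be initiated 48 h following the discontinuation of nasal continuous positive airway pressure". The Methods part of the abstract agrees: "the intervention will initiate 48 h after discontinuing nasal continuous positive airway pressure".
- **Non-invasive ventilation.** The explanation for the choice of comparators {6b} justifies the late arm by studies that waited 48 h from the end of non-invasive ventilation. The background {6a} lists the same candidate start time in the same terms. The key to Table 2 gives "t1 started to feed; t2 after 48 h of discontinuing non-invasive ventilation".

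The inclusion criteria {10} show that the two terms are not interchangeable: "Requirement non-invasive ventilation support, including the use of a high-flow nasal cannula". High flow alone is enough to qualify, and CPAP is not required.

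The late-arm section also says that the arms are otherwise identical, "with the sole distinction being the difference in the start time".

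**The concern.** In this trial the start rule is the whole experimental contrast. Content, duration, frequency and stopping rule are shared, so a loosely defined late start means a loosely defined comparator.

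Two kinds of infant are exposed. One receives high flow but never CPAP; the event that starts the 48 h never occurs. The other is stepped down from CPAP to high flow; the operative text can start the intervention while the infant is still on what the eligibility criteria call non-invasive support, whereas the other wording waits until that support has ended.

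For both, the same start date could be judged compliant under one sentence and not under another. That affects what the late strategy means, how fidelity is checked, and who belongs in the per-protocol analysis that {20a} plans alongside the main one.

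**Working it through.** The article gives no figure to reproduce. The check applies each rule to each possible support history.

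**Inputs**
- Rule A (late OMIs group section, abstract): start = end of CPAP + 2 days.
- Rule B (comparator rationale, background, timeline key): start = end of non-invasive ventilation + 2 days, with high flow counted as non-invasive support under {10}.
- Frequency and length (early OMIs group section, which applies to both arms): "It will be conducted once a day", 15 min each time.
- d = days on high flow after CPAP ends. The article gives no value.

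**Application**

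| Support history | Rule A | Rule B | Difference |
|---|---|---|---|
| CPAP is the only or last support | CPAP end + 2 | CPAP end + 2 | none |
| CPAP, then high flow for d days | CPAP end + 2 | CPAP end + d + 2 | d days |
| High flow only | no trigger event | high-flow end + 2 | Rule A undefined |

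In the middle row the difference is (CPAP end + d + 2) − (CPAP end + 2) = d days. At one session a day this is up to d sessions, or up to 15 × d minutes. It is a ceiling because sessions stop once full oral feeding has been held for 48 h.

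**How much rests on the timeline key.** The body of Table 2 is not shown, and t2 is a label, not an instruction. Reading it as the late start is an inference, supported by the shared 48 h and by t1 matching the early-arm rule ("The intervention will start once the infant begins to receive milk and exhibits stable vital signs"). The conflict does not depend on it: the comparator rationale and the background use Rule B in plain words. The high-flow-only gap needs only the eligibility criteria and the late-arm section.

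**What is not affected.** The primary outcome counts days from the initiation of feeding, not from the first OMI session, so neither rule moves its clock. Under {20a} the main analysis is by assigned group, whatever intervention was received.

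**The case against.** The best reply is that CPAP is loose shorthand. Three places, including the section that justifies the comparator, use the broader term, so a careful reader can recover the likely intent. That stands, and it rules out saying that the late strategy cannot be reproduced. It does not rescue the operative sentence, because the eligibility criteria name high flow expressly and the shorthand fails for those infants.

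A second reply is that staff receive "standardized training in accordance with the research manual". The manual is not shown and may well give a single working rule, so one should not infer that nurses have none. The published statements would still disagree.

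A third is that no harm to the result is shown. This is largely right. A reader might infer that the primary comparison is biased or loses power; the documents do not support that, for the reasons given about the clock and the intention-to-treat analysis. A reader might also take late-arm enrolment as the number affected: 12 infants a month {15} at 1:1 allocation {14} gives 12 × 1/2 = 6 a month. That is everyone entering the arm, not those with a high-flow-only or step-down course, for whom no share is given.

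Finally, the article names a per-protocol set without defining it. The definition may sit in an analysis plan that is not shown, and its absence is not part of this point.

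**Conclusion.** The point holds as an internal contradiction in the rule that separates the arms. The operative text gives no late start for an eligible infant on high flow only. For an infant stepped down from CPAP it gives a start d days earlier than the rule the protocol itself justifies, worth up to d daily sessions. The rules agree when CPAP is the last or only support.

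The number affected is unknown, and no effect on transition time or power is claimed. What suffers is the definition of the late strategy and of adherence to it. The conclusion assumes that the inclusion criterion means what it says about high flow and that no unseen document overrides the printed text. It should be fixed because the contrast rests on it and the repair is small.

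**What to change.** 1. In the late OMIs group section, replace the reference to nasal CPAP with the end of all non-invasive ventilation support, including high-flow nasal cannula. This agrees with the background, the eligibility criteria, the comparator rationale and the timeline key. Use the same wording wherever the rule is restated.
2. For each late-arm infant record the date and time of CPAP end (if CPAP was used), of the end of all non-invasive support, and of the first OMI session, unless these are already captured.
3. Judge per-protocol adherence of all late-arm infants, including those already enrolled, against that single rule. Classifying each infant by whichever rule was applied would be circular, since a start under either would then count as adherent.

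The cost is a short amendment, brief retraining of the charge nurses and a little extra data capture. There is a real downside: stepped-down infants will start later and may receive fewer sessions than under the CPAP wording, and some already enrolled may become deviations in the per-protocol set. The intention-to-treat set is unchanged.

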#### Criteria for discontinuing or modifying allocated interventions {11b}

Modifying the allocation intervention is expected to be unlikely. Nevertheless, parents have the option to remove their preterm infant from the study at any time for any reason.

#### Strategies to improve adherence to interventions {11c}

Every possible endeavor will be undertaken to maintain the authenticity of the intervention. Before the study begins, individuals participating in the research will receive standardized training in accordance with the research manual. Only after passing the assessment will they be allowed to join the study. Any divergence from the protocol will be meticulously recorded, with an intervention fidelity checklist being completed by the research nurse at the conclusion of the procedure.

#### Relevant concomitant care permitted or prohibited during the trial {11d}

To ensure the accuracy and comparability of trial results, during the study, other unrelated oral motor rehabilitation treatments will be prohibited.

#### Provisions for post-trial care {30}

Patients and their families will receive free consultation and follow-up during and after the research.

#### Outcomes {12}

##### Primary outcome

Transition time is defined as the number of days needed to progress from the initiation of feeding to the establishment of full oral feeding. In this study, full oral feeding is defined as achieving a feeding volume of 120 ml/(kg/day) without the necessity for tube feeding for at least 48 h [20]. The corrected gestational age (PMA) will be recorded both at the initiation of oral feeding and upon the achievement of full oral feeding.

##### Secondary outcomes

**Feeding performance**

This includes feeding efficiency, defined as the average milk intake per minute, and feeding effectiveness, which is the milk intake orally within the first 5 min divided by the ordered milk volume. Feeding performance will be observed at two distinct time points: the day on which full oral feeding is achieved and the day of discharge. Nursing staff who are not involved in the study will record the volume of oral intake and the duration of feeding, from which they will calculate both the feeding efficiency and effectiveness.

**Oral motor function**

The neonatal oral-motor assessment scale (NOMAS) will be used to evaluate the oral motor function of the study subjects. This scale evaluates the jaw and tongue function of newborns across three dimensions: normal sucking, disorganized sucking, and sucking disorders. Evaluations will be performed at baseline, weekly, upon achievement of full oral feeding, and at the time of discharge. The assessment is scheduled to take place daily between 9 a.m. and 10 a.m. During each assessment, the evaluator will also be required to record a 2-min assessment video for documentation and further analysis purposes.

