## Statistical methods

### Statistical methods for primary and secondary outcomes {20a}

The intention-to-treat analysis (ITT) will be the main analysis, with a per-protocol set (PPs) analysis conducted simultaneously. A significance level of *P* < 0.05 will be considered statistically significant. In the ITT analysis, all subjects will be included in the group to which they are assigned, regardless of whether they completely received the intervention. (1) Descriptive statistics will be used to summarize baseline characteristics. Continuous variables will be presented as Mean ± Standard deviation and categorical variables as percentages (%). (2) For comparisons between groups, Student *t*-tests will be applied for continuous variables, and chi-square tests will be utilized for categorical variables. (3) Assessment of efficacy: for continuous variables, independent Student *t*-tests will be employed for evaluation if conditions are met. (4) For data that do not follow a normal distribution, ordinal data, or data with significantly unequal variances, non-parametric tests will be used. The statistical analysis will be conducted using the medical statistical software SPSS 23.0 (SPSS, IBM Corporation, Armonk, NY, USA).

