### Methods for additional analyses (e.g., subgroup analyses) {20b}

The sub-group analysis based on gestational age will be performed. If required, according to the type of variable and their distributions, linear or logistic regressions will be performed. Multivariate regressions will also be conducted for selected outcomes, if necessary. In cases where a baseline characteristic in the enrolled population differs between the two groups with a *P* < 0.05 in the univariate analysis, then the results will be adjusted for that variable).

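### Baseline NOMAS is collected but is not a prespecified covariate: adjustment is required only after a baseline difference at P < 0.05, so the comparison of later oral motor scores gives up precision

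*Protocol article*

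**What the plan says.** The protocol article, under Oral motor function, schedules the same scale before and after the intervention starts: "Evaluations will be performed at baseline, weekly, upon achievement of full oral feeding, and at the time of discharge".

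The between-arm methods are in section {20a}. They are general and do not name NOMAS:
- Continuous outcomes: "for continuous variables, independent Student *t*-tests will be employed for evaluation if conditions are met".
- Categorical outcomes: "chi-square tests will be utilized for categorical variables".
- Ordinal or non-normal data, and "data with significantly unequal variances, non-parametric tests will be used".

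No change score, analysis of covariance or repeated-measures model is stated.

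Section {20b} offers three routes to a covariate. The only mandatory one applies when a baseline characteristic differs between arms at P < 0.05: "then the results will be adjusted for that variable". The other two are discretionary and name neither an outcome nor a covariate: "If required, according to the type of variable and their distributions, linear or logistic regressions will be performed", and "Multivariate regressions will also be conducted for selected outcomes, if necessary".

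**The concern.** The baseline value of an outcome is often among its best predictors. If it is left out, differences between infants in initial oral motor maturity stay in the error term. The trial already pays for the measurement, so the only cost of using it is a line of analysis wording.

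The rule in {20b} selects covariates by the wrong criterion. Under randomisation a baseline difference at P < 0.05 arises by chance in about 1 trial in 20, whether or not the variable predicts the outcome. A strongly prognostic baseline with a modest imbalance is left out, and a useless one with a large imbalance is brought in. The discretionary routes leave the choice until the data can be seen.

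At stake is the precision of one named secondary outcome, the function that the intervention targets. The primary outcome is not affected.

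**Working it through.** **Inputs.** The article gives no planning figure for NOMAS. Its only sample size, in section {14}, is for transition time: 126 per arm, raised to 140 for 10% dropout (126/0.9 = 140). I use 126 only as a plausible number of evaluable infants per arm. The stated inputs (difference 13.40 − 11.36 = 2.04 days, SD 4.99, 5% two-sided, 80% power) give 94 per arm; 126 is what they give at 90% power. That mismatch is a separate matter and does not bear on this point.

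Assumptions, not in the article: r from 0.1 to 0.6, approximately normal scores, a two-sided 5% test.

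**Precision.** Adjusting for baseline multiplies the variance of the arm comparison by 1 − r², so the SE is multiplied by √(1 − r²) and the effective n per arm is 126/(1 − r²). Unadjusted, the SE of a standardised difference is √(2/126) = 0.126 SD. Power is Φ(d/(0.126·√(1 − r²)) − 1.96). It is shown for d = 0.353, which gives 80% unadjusted ((1.96 + 0.842) × 0.126), and for an illustrative d = 0.30.

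| r | Variance saved | SE factor | Effective n per arm | Power, d = 0.353 | Power, d = 0.30 |
|---|---|---|---|---|---|
| 0 | 0% | 1.000 | 126 | 80.0% | 66% |
| 0.1 | 1% | 0.995 | 127 | 80.4% | 67% |
| 0.3 | 9% | 0.954 | 138 | 83.6% | 70% |
| 0.5 | 25% | 0.866 | 168 | 89.9% | 79% |
| 0.6 | 36% | 0.800 | 197 | 93.8% | 85% |

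**Does the P < 0.05 rule recover this?** A simulation with 126 per arm, d = 0.353, normal scores and 10,000 trials per setting compared three strategies. The r = 0.7 row lies beyond the assumed range and is shown as an extreme case.

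| r | Rule triggered | Never adjust | Rule in {20b} | Always adjust |
|---|---|---|---|---|
| 0.3 | 5.1% | 79.0% | 79.4% | 82.4% |
| 0.5 | 5.1% | 80.0% | 81.0% | 89.7% |
| 0.7 | 4.9% | 80.0% | 81.9% | 97.3% |

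The rule stays within two points of never adjusting. With no true effect, always adjusting kept the false-positive rate at 4.6% to 5.1%.

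**An imbalance that the rule misses.** A baseline difference of 1.5 SE has P of about 0.13 and size 1.5 × 0.126 = 0.189 SD. In a trial with that imbalance, the expected shift in the unadjusted later difference is r × 0.189: 0.02 SD at r = 0.1, 0.06 at 0.3 and 0.11 at 0.6, against an SE of 0.126.

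**The case against.** **The baseline might still be used.** A reader might infer that the baseline score simply goes unused, or enters only after a significant imbalance. The article does not support that. Section {20b} also allows regression at discretion, and nothing in {20a} rules out testing change from baseline. This stands, and the point is limited to the lack of prespecification. A change score would not be an adequate substitute: with equal SDs its variance factor is 2(1 − r), which is 1.4 at r = 0.3, 1.0 at 0.5 and 0.8 at 0.6, against 0.91, 0.75 and 0.64 with adjustment.

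**Covariates for a secondary outcome belong in the analysis plan.** Silence on covariates would be no finding. Here the article is not silent: it states the tests and a rule for when adjustment is required, and that rule is poor. The rule covers every outcome. NOMAS is the case where the outcome's own baseline is explicitly scheduled.

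**Bias.** A reader might also infer that the unadjusted comparison is biased, or that a chance imbalance would pass as an effect of start time. Neither follows. Over repeated randomisation the unadjusted test is unbiased, and its SE and 5% error rate already allow for chance imbalance. The shifts above describe single trials with that imbalance.

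**The gain may be small.** This stands. Infants are enrolled within 72 h of life on non-invasive support, so baseline scores may vary little. Scores at full oral feeding and discharge may also be compressed. At r = 0.1 power moves only from 80% to 80.4%. If NOMAS is analysed as categories of sucking pattern, 1 − r² is only approximate.

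**A careless baseline could do harm.** This stands too. The arms differ in when the first session occurs: at the start of milk intake, or 48 h after nasal CPAP ends. With weekly scoring, the last score before the first session could in the late arm be a later, post-randomisation one from a more mature infant. Adjusting for it could distort a comparison that is otherwise unbiased.

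**Conclusion.** The concern holds as one of precision on a secondary outcome. Baseline NOMAS is scheduled, the stated tests have no place for a covariate, and the only mandatory route to adjustment is a baseline significance test that recovers almost none of the available gain. The loss is about r² of the variance: 1% to 36% for an assumed r of 0.1 to 0.6, equivalent to 127 to 197 infants per arm in place of 126, and nothing if r is near zero. The size rests on assumed r and d, on approximately normal scores, and on a sample size planned for another outcome. Validity is not in question. The change is worth making because it costs almost nothing and removes a data-dependent choice.

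**What to change.** In {20a}, state that NOMAS at each later time point is compared between arms with a model containing arm and the scheduled baseline NOMAS, whatever the baseline P value. Use a linear model for a continuous score, and rank ANCOVA, a proportional-odds model or a logistic model if the score is non-normal, ordinal or categorical.

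Define the baseline as the scheduled baseline assessment under Oral motor function, taken at the same point in both arms, at or before randomisation and before any OMI. Do not define it as the last assessment before the first OMI session, because that timing differs by arm. Keep infants without a scorable baseline by a missing indicator. In {20b}, exempt this covariate from the P < 0.05 rule.

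The cost is a few sentences of analysis wording. The assessment is already scheduled and SPSS fits these models. No infants or procedures are added, provided that the scheduled baseline already falls at or before randomisation. If it does not, its timing has to be fixed as well.
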